### Quality control

To improve quality control during the trial process, several measures will be taken. (1) Before clinical research, we will conduct a unified training for all researchers about the trial protocol, operating standard procedures, and personnel deployment. (2) To ensure the feasibility of the research operation, all the acupuncturists involved have obtained the qualification certificate for more than 5 years, and have grasped the operating specifications of the new needle equipment. (3) Instruments, equipment, and reagents to be used have strict quality standards to ensure that they work under normal conditions. (4) To ensure the reliability of the research conclusions, information feedback is carried out at the beginning and mid-term of the project, and we will solve various problems in the course of the project research promptly.

## Discussion

The individual's social role is always changed as a result of sudden neurological impairment after stroke, which requires a psychological transition and adjustment to a new definition of self (62–65). The self-acceptance process causes a high incidence of anxiety. The incidence of anxiety did not decrease significantly over time during 24 months after stroke (66). During COVID-19, PSA showed a noticeable peak (9). It has been pointed out by two comprehensive reviews that loss, social isolation, uncertainty, and physical dependence as factors that might contribute to negative psychological outcomes (67). Emotional resistance and self-acceptance are associated with poorer recovery outcomes and reduced life engagement. Since the long-term anxiety exerts a negative effect on the quality of life for the stroke survivors, which has become a worldwide phenomenon (68), it deserves more attention than it has so far received.

There has been a large number of studies showing that acupuncture is effective in the treatment of stroke and its complications. Acupuncture interventions are various, and a unified acupuncture protocol is still on the way (69). Jin's three-needle therapy (JTNT), invented by [name], is famous for using three silver needles to cure diseases. JTNT is representative and has been widely used in public hospitals around Southern China. Its real clinical efficacy is worthy of study (70). Despite the high number of clinical trials about stroke, the focus of most existing research is limited to motor symptoms rather than complications after stroke (20). Besides, there is few sham control to observe the real effect of acupuncture. Investigators focus on efficacy rather than exploring pathogenesis. Given this, this study selected the sham needle equipment invented by members of our research team as the control interventions. We formulated a standard operating procedure protocol to further expound the mechanism of acupuncture through ELISA and rs-fMRI.

The clinical effect of JTNT on both motor and anxiety symptoms for PSA has been verified in the previous clinical trial carried out in the First Affiliated Hospital of Guangzhou University of TCM. To further explore the mechanism of JTNT, we completed the first draft of this research protocol. After discussion and revision of the draft by the hospital ethics committee, the final protocol was unanimously approved.

This trial attempted to assess possible mechanisms of JTNT for PSA by the HPA axis. To dynamically observe the therapeutic effect of acupuncture on PSA, we detected the key factors of the HPA axis–the changes in ACTH and CORT before and after treatment. The action mechanism of JTNT is investigated by functional magnetic resonance imaging (fMRI) to observe whether JTNT can relieve anxiety symptoms by activating the core brain regions associated with emotion regulation.

However, this study still has limitations. First, this is a single-center study, because of the COVID-19 outbreak, we cannot conduct trials in multiple centers. Secondly, due to the use of a new type of acupuncture equipment in this study, it is necessary to explain to the patient well in exchange for greater compliance. In addition, we are still working hard to standardize the process of this study to provide high-quality medical evidence for JTNT so that it can be used as an optimized plan for PSA supplementation therapy.

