It is indispensable to identify the cause and pathogenesis of PSA for targeted therapies. According to the available research results, PSA is multifactorial, involving biological and neurophysiological factors. The hypothalamic-pituitary-adrenal (HPA) axis is one of the neuroendocrine systems in the brain that controls the release of glucocorticoids from the adrenocortical glands (23). As well as being a component of the stress response, it also mediates additional downstream pathophysiological changes (24). Hypothalamic hormones stimulate corticotroph cells in the anterior pituitary to secrete adrenocorticotropin (ACTH) (25, 26). ACTH activates the synthesis and secretion of glucocorticoid cortisol (CORT) by the human adrenal cortex (27, 28). As a result of the variety of releasing factors, the HPA axis is expected to respond to stimulation quickly and dynamically. Clinical studies suggest that immediately after stroke onset, a massive release of pro-inflammatory cytokines activates the HPA axis (29, 30). The activated HPA axis promoted a “systemic anti-inflammatory response” that negatively affects function recovery and anxiety generation (31). Besides, anxiety and depression are recognized to be associated with dysregulation of the HPA axis, which accentuates inflammation, consequently increasing the risk of stroke recurrence (32). Dysfunction of the HPA axis is suspected to be one of the main mechanisms connecting stroke with anxiety (33). This study provides preliminary biological evidence for the potential efficacy effect of acupuncture on PSA.

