### The secondly outcome

The secondary outcomes are the physical recovery and daily quality of life for patients with PSA, which are evaluated by the National Institute of Health stroke scale (NIHSS) and the Modified Barthel Index Scale (MBI). Besides, secondary outcomes will be obtained using ELISA and fMRI scanning. ELISA will be used for quantitative analysis of the content of CORT and ACTH in serum.

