### Statistical analysis

#### Clinical data analysis

Third-party statisticians who do not involve in the whole assignment process and implementation of the trial will be invited to conduct statistical analysis. The data will be analyzed using SPSS 26.0 software (SPSS, Inc., Chicago, IL, USA) according to the intention-to-treat principle. The multiple imputation-expectation maximization algorithms are conducted to impute missing data. Continuous variables are summarized as mean ± standard deviation (SD) and tested using a *t*-test or Wilcoxon rank-sum test analysis. Categorical variables are reported in percentage (%) and compared using Pearson's *X*^2^ test or Fisher's exact test. The groups' comparisons are analyzed by *t*-test (independent *t*-test for comparison between the groups; paired *t-*test for comparison within the same group). The non-parametric Wilcoxon rank-sum test or the Mann-Whitney U test will be conducted for the measurement data without a normal distribution or homogeneous variance. All bilateral hypothesis tests with a significance level <0.05 will be considered statistically significant.

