#### MRI data analysis

The DPARSF software platform (DPARSF, Data Processing Assistant for rs-fMRI, GNU GENERAL PUBLIC LICENSE, Beijing, China) is used to preprocess the MRI data, based on the Resting-State fMRI Data Analysis Toolkit (REST; http://www.restfmri.net) and the statistical parametric mapping (SPM8; http://www.fil.ion.ucl.ac.uk/spm). Then, the rs-fMRI data corrections are performed on the images such as slice timing and realignment for intra-volume acquisition delay. To minimize the influence of head movement, subject with head motion (maximum displacement > 2.5 mm or angle movement > 2°) during the whole fMRI scan will be excluded. Stabilization of the magnetization and adaptation of the participants to the fMRI environment will take time. For each time series, the first 10 time points will be deleted to exclude non-neuronal BOLD noise signals (59). In spatial normalization, the whole brain template of the Montreal Neurological Institute (MNI) standard space is normalized in all data spaces (isotropic voxel size = 3 × 3 × 3 mm) (60). By calculating Kendall's coefficient of concordance (KCC), a voxel-by-voxel basis of a given voxel time series with its neighboring 26 voxels is generated to obtain a separate ReHo map. Finally, a spatially smoothed function with 4 × 4 × 4 mm (full width at half maximum) Gaussian kernel is applied to reduce the noise and residual in the gyrus anatomy. The statistical analysis tool of REST is performed for independent *t*-tests to identify the ReHo patterns of the three groups (61). Besides, a paired *t*-test is applied to compare the changes in the brain before and after the treatment in each group. Covariates, such as age and education, are considered by the Pearson correlation coefficient to analyze the relationship between the improvement scores of the correlation scales and the brain regions of fMRI image data.

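### The HPA-axis reading is allowed to rest on before/after change in ACTH and cortisol within an arm, which cannot separate a JTNT effect from change common to all arms

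*Protocol article*

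**What the plan says.** The Introduction gives the rationale: "Dysfunction of the HPA axis is suspected to be one of the main mechanisms connecting stroke with anxiety". It claims only a modest level of evidence: "This study provides preliminary biological evidence for the potential efficacy effect of acupuncture on PSA". The Discussion returns to the aim, "This trial attempted to assess possible mechanisms of JTNT for PSA by the HPA axis", and says how it is pursued: "we detected the key factors of the HPA axis–the changes in ACTH and CORT before and after treatment".

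The serum outcome is secondary and is defined as a measurement: "ELISA will be used for quantitative analysis of the content of CORT and ACTH in serum". No separate serum analysis is given, so the general rules in Clinical data analysis apply: "independent *t*-test for comparison between the groups; paired *t-*test for comparison within the same group", with rank tests where the data are not normal. The between-group test is not adjusted for baseline.

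Only the imaging data are linked to symptoms. MRI data analysis plans a Pearson correlation "to analyze the relationship between the improvement scores of the correlation scales and the brain regions of fMRI image data".

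**The concern.** A paired test asks whether the mean marker change in one arm is zero. It uses no control arm, so anything that moves the hormone over four weeks counts as a finding. The article itself supplies reasons to expect such movement. The Introduction says that after stroke onset "a massive release of pro-inflammatory cytokines activates the HPA axis". The Inclusion criteria admit patients 2 weeks to 3 months after stroke. Interventions and comparison gives all three arms drugs and rehabilitation.

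A lower cortisol level at week 4 in the JTNT arm could therefore be read as support for an HPA mechanism when needling did nothing to the axis. The randomised comparison that would answer the question is in the plan, but it is not given priority, and the Discussion describes the evidence in before/after terms.

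**Working it through.** **1. The article's own figures.** Sample size gives HAMA 14.25 ± 7.10 (JTNT) and 19.46 ± 4.80 (sham), two-sided alpha 0.05 and power 0.90.
- Difference: 19.46 − 14.25 = 5.21.
- Root-mean-square SD: √((7.10² + 4.80²)/2) = 6.06. Standardised difference: 5.21/6.06 = 0.86.
- The printed formula gives (1.960 + 1.282)² × 2 × 6.06²/5.21² = 28.4, so 29. The noncentral t calculation gives 30 (power 0.906).
- 30/(1 − 0.20) = 37.5, so 38 per arm, and 3 × 38 = 114.

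The stated 30, 38 and 114 reproduce. They concern HAMA only. They are used here for the number per arm: 30 evaluable, 38 randomised.

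**2. The paired test under a change common to all arms.** Let the marker change in every arm have mean s, in units of the SD of the change score, with no JTNT effect. The article gives no ACTH or CORT values, so s = 0.3 and s = 0.5 are assumptions. The paired t statistic has n − 1 degrees of freedom and noncentrality s√n.

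| n per arm | s | s√n | critical t | chance that p < 0.05 in the JTNT arm |
|---|---|---|---|---|
| 30 | 0.3 | 1.643 | 2.045 | 36% |
| 30 | 0.5 | 2.739 | 2.045 | 75% |
| 38 | 0.3 | 1.849 | 2.026 | 44% |
| 38 | 0.5 | 3.082 | 2.026 | 85% |

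Simulation agrees with these values to within about one or two percentage points.

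**3. The JTNT-sham test in the same situation.** The common change cancels: s − s = 0. The test therefore keeps its nominal 5%, and simulation gave 0.050 to 0.052.

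**4. Why adjust for baseline.** With equal variances at both visits and baseline to week-4 correlation ρ, the residual variance is proportional to 1 for week-4 values alone, 2(1 − ρ) for change scores and 1 − ρ² for ANCOVA. At an assumed ρ = 0.5 these are 1, 1 and 0.75. ANCOVA also removes chance baseline differences between the arms.

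**The case against.** The strongest reply is that the article claims little. It states no hypothesis that hormone change explains anxiety relief. It speaks of possible mechanisms and preliminary evidence, and its one explicit hypothesis is clinical. The between-group test and both control arms are already there. The assumed fall of 0.3 to 0.5 SD has no source, and the activation described is immediate, while patients enter at 2 weeks or later. Finally, a condensed article may leave exploratory biomarker models to an unseen analysis plan.

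Most of this stands, and it limits the point. It does not remove it, because the within-arm test and the before/after reading are stated in the article, not merely left out of it.

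A reader might infer something stronger: that the serum plan is invalid because ACTH and CORT are never related to HAMA or GAD-7, so that any mechanism result would be false. The documents do not support that, for three reasons.
- No mediation null is stated, so the planned tests do not fail a stated one.
- If needling really moved cortisol by an assumed 0.5 SD without any link to anxiety, the JTNT-sham test would be significant in about 48% (n = 30) or 57% (n = 38) of trials. That is the power of a valid randomised test to detect a real shift, not an error rate.
- Requiring an association as well would not secure the claim. Serum and scales are taken together at week 4, so the hormone may follow the anxiety. In a simplified simulation (4,000 runs), JTNT lowered anxiety by 0.86 SD and the marker merely followed it. The arm contrast and the arm-adjusted association were then both significant in 37% (n = 30) and 46% (n = 38) of trials at an assumed correlation of 0.5, and in 64% and 74% at 0.7. With true mediation (assumed 0.5 SD shift, slope 0.3) both were significant in only 30% and 43%.

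**Conclusion.** The point holds as an analysis choice that should be corrected: within-arm change in ACTH and CORT should not carry the HPA-axis reading. The structural argument needs no assumed effect size, because a paired test in one arm cannot tell a JTNT effect from change shared by all arms.

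The size does rest on assumptions. A common change of 0.3 to 0.5 SD of the change score would make the JTNT-arm paired test significant in about 36% to 75% of trials (n = 30) or 44% to 85% (n = 38), against about 5% for JTNT versus sham. With no common change, the paired test too would be at about 5% when JTNT has no effect.

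The lack of a serum-symptom analysis is a gap that may be filled, not an error. Only secondary, exploratory conclusions are touched. The primary efficacy comparison and the sample size are not.

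**What to change.** In Clinical data analysis, name the JTNT-sham contrast of week-4 ACTH and CORT, adjusted for the baseline level (ANCOVA), as the test of an effect on the HPA axis. State that the within-arm paired tests are descriptive.

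In the Discussion, limit the conclusion to whether JTNT changed ACTH or CORT relative to sham.

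Optionally, in line with what is planned for fMRI, add an exploratory association of marker change with HAMA change, adjusted for arm. The adjustment matters: with no within-arm link, a crude correlation pooled over the JTNT and sham arms was significant in 7% to 21% of simulated trials at 30 per arm, for assumed marker shifts of 0.3 to 0.8 SD. Describe the result as supportive only. It cannot exclude reverse direction or confounding, and it should neither gate nor establish a mechanism claim.

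The text gives serum sampling at baseline and week 4 only, while Table 1 also marks weeks 8, 12 and 16. Reconcile these in the same edit. Baseline and week 4 are common to both, so the proposed contrast does not depend on the answer.

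The cost is a few sentences and one model per marker (one more each if the association is added), with no extra patients or samples. The mechanism statement becomes slightly more cautious.

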## Ethics statement

The studies involving human participants were reviewed and approved by Ethics Committee of the First Affiliated Hospital of Guangzhou University of Traditional Chinese Medicine. The patients/participants provided their written informed consent to participate in this study. Written informed consent was obtained from the individual(s) for the publication of any potentially identifiable images or data included in this article.

